#### Exclusion criteria

Patients with any of the following conditions will be excluded: irritable bowel syndrome or constipation secondary to organic diseases (e.g. endocrine, metabolic, or postoperative diseases); abdominal aneurysms, hepatosplenomegaly, or serious cardiovascular, liver, kidney, or psychiatric diseases; and blood coagulation disorders. Also excluded are pregnant or lactating women and patients requiring administration of anticoagulant agents, such as warfarin or heparin. Participants treated with antiplatelet treatments, such as aspirin or clopidogrel, for the secondary prevention of cerebral infarction are eligible.

### Intervention

The three groups will receive routine health care and secondary prevention as for all other inpatients with ischemic stroke. These treatments include antiplatelet therapies, antihypertensive therapies, glucose control, dyslipidemia control, and dehydration treatments, if necessary. For participants with no SBMs over 4 or more days, use of laxatives (regarded as emergency drugs, such as bisacodyl, glycerin enema etc.) will be permitted as an emergency measure to promote defecation. All information regarding the use of emergency drugs (including date of administration, and laxative types and dosage) will be recorded. Before the initiation of the study, all researchers will receive standardized training regarding the content of the trial, treatment strategies, assessments, and quality control. Interventions will be performed in accordance with the STRICTA [25] and good clinical practice guidelines.

#### Acupuncture group

All the study acupuncturists will be registered practitioners of traditional Chinese medicine with at least 5 years’ clinical experience, as well as a medical education background. The acupuncture treatments and manipulations will be standardized among acupuncture practitioners through live and recorded training. Outpatients will receive treatment in clinics and inpatients will be treated in wards. If inpatients are discharged, they will receive acupuncture in clinics by the same acupuncture practitioner. Sterile needles (size 0.30 × 40 mm and 0.35 × 75 mm; Guizhou Ande Medication Appliance, Ltd., Guiyang City, Guizhou Province, China) will be used.

For the acupuncture, we will use Wang’s classical 10 acupoints formula. These acupoints have been selected and combined for gastrointestinal disease after a stroke based on the clinical experience of an accomplished Chinese acupuncturist, Leting Wang, in the 1960s [26, 27]. The 10 acupoints include CV13 (*shangwan*), CV12 (*zhongwan*), CV10 (*xiawan*), bilateral ST25 (*tianshu*), CV6 (*qihai*), bilateral PC6 (*neiguan*), and bilateral ST36 (*zusanli*). All of the acupoints will be located according to the World Health Organization Standardized Acupuncture Points Location [28]. After sterilizing the skin, needles will be slowly and vertically inserted into ST25 (*tianshu*) bilaterally, without any manipulation. Needle insertion will stop upon piercing of the muscle layer of the abdominal wall (nearly 20 to 60 mm subcutaneously). Known side effects of needle insertion include mild soreness. Other needles will be inserted to a depth of 10–25 mm to predetermined acupoints and manually manipulated by rotation to produce the characteristic sensation of *deqi*. The *deqi* sensation is also called *needle sensation*, and refers to perceived subcutaneous tension around the needle, which is felt by the acupuncture practitioner, and soreness, numbness, distension, and heaviness around the acupuncture point that is felt by the participant. Each session will last for approximately 30 min. All needles will be removed with sterile cotton balls to avoid bleeding.

Each participant will be treated once a day and will receive 16 treatment sessions in total over 4 consecutive weeks. Treatment will be conducted 5 times per week in the first 2 weeks and 3 times per week in the last 2 weeks.

#### Medication group

Participants in the medication group will receive 5 mg of mosapride citrate, 3 times per day for 4 consecutive weeks. Unused tablets will be collected by the researchers at the end of the treatment period.

#### Control group

Participants in the control group will receive routine health care and secondary prevention treatments for ischemic stroke. For participants with no SBMs over 4 or more consecutive days, cathartic treatment will be given. Details related to the usage of cathartic drugs will be recorded during the trial.

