#### Follow-up

After the 4-week treatment, all participants will enter an additional 4-week follow-up period. During this time, they will receive routine health care and secondary prevention as provided to all other patients with ischemic stroke. Laxatives will be allowed for use as emergency drugs during the follow-up period. However, acupuncture treatment and mosapride citrate are not permitted during follow-up.

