### Outcome measures

#### Primary outcome measure

The primary outcome measure will be the change in the weekly mean number of CSBMs over the 4 weeks of the intervention and the 4 weeks of the follow-up. A CSBM is defined as a SBM unrelated to the administration of laxatives or finger manipulation, accompanied by a self-reported feeling of complete evacuation. Bowel movements achieved with the help of glycerin, enemas, or finger manipulation are not considered spontaneous. If bowel movements occur within 24 h after the intake of laxatives, they will not be considered spontaneous. However, if bowel movements occur more than 24 h after administration of laxatives, they will be considered spontaneous. The total number of CSBMs during the treatment period and follow-up period will be averaged to obtain mean weekly CSBMs.

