#### Secondary outcome measures

The change in the number of mean SBMs that are unrelated to the administration of laxatives or finger manipulation, with or without a self-reported feeling of complete evacuation. This measure will be calculated in the same way as the CSBMs.The change in mean stool consistency score, as per the Bristol Stool Scale (Table 1). The score will be recorded according to the stool type (e.g. type 1 = 1 point, type 2 = 2 points, etc.) to obtain mean stool consistency scores. The Bristol Stool Scale is a widely used form authored by Dr. K Heaton, reader in medicine, University of Bristol. It can be downloaded from the website https://www.bladderandbowel.org/bowel/bowel-resources/bristol-stool-form-scale/ representations of the different types of stool will be included in the patients’ diaries and serve as visual comparators. A patient will record the type of stool in their diary according to the picture.The change in mean straining scores during defecation. The severity of straining will be graded using a 5-point ordinal scale: 0 = absent, 1 = mild, 2 = moderate, 3 = severe, and 4 = very severe.The change in weekly frequency of laxative use. This includes the total number of times that laxatives are used during the 4-week treatment period and the 4-week follow-up period. Instances of laxative use will be summed and divided by 4 to obtain the weekly frequency during the two periods.

**Table 1 Tab1:** Bristol Stool Scale

Type	Description
1	Separate hard lumps, like nuts (hard to pass)
2	Sausage-shaped, but lumpy
3	Like a sausage but with cracks on its surface
4	Like a sausage or snake, smooth and soft
5	Soft blobs with clear-cut edges (passed easily)
6	Fluffy pieces with ragged edges, a mushy stool
7	Watery, no solid pieces; entirely liquid

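### The rescue-laxative rule for the treatment period is worded as permissive for all three groups but directive for control, which can shift one secondary outcome without any treatment effect

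*Protocol article*

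**What the plan says.** All places are in the protocol article, Methods/design.

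- **Intervention (all three groups).** The trigger and drugs are introduced with "For participants with no SBMs over 4 or more days, use of laxatives", which are described as emergency drugs. Their use "will be permitted as an emergency measure to promote defecation". Date, type and dosage are to be recorded.
- **Control group.** "For participants with no SBMs over 4 or more consecutive days, cathartic treatment will be given". A further sentence asks for details of cathartic use to be recorded.
- **Acupuncture group and Medication group.** Neither section has a rescue sentence of its own, so only the common rule applies to them.
- **Follow-up.** "Laxatives will be allowed for use as emergency drugs during the follow-up period". This covers all participants in the same words.
- **Primary outcome measure.** Of bowel movements within 24 h after a laxative, the article says "they will not be considered spontaneous". Later movements do count.
- **Secondary outcome measures.** One of them is "The change in weekly frequency of laxative use", summed and divided by 4 for each 4-week period.
- **Discussion.** Therapists and participants are not blinded.

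**The concern.** During treatment, control participants fall under two statements, one making rescue optional and one making it automatic. The other two arms fall only under the optional one. Those who give or take rescue know the arm, so they know which sentence applies. Blinding the data managers and statisticians does not help, because any difference arises before the data reach them.

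Rescue use is itself an outcome. If staff follow the control sentence literally, laxative use in control can exceed that in the other arms when bowel function is identical, and the excess would be read as a laxative-sparing benefit of acupuncture or mosapride. The trial is meant to supply effect sizes for later trials, so a distorted estimate could be carried forward.

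**Working it through.** **1. The two statements side by side**

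| Element | Intervention (all groups) | Control group section |
|---|---|---|
| Trigger | no SBM over 4 or more days | the same, with *consecutive* added |
| Obligation | permitted | will be given |
| Term for the drugs | laxatives, as emergency drugs | cathartic treatment |
| Period | not limited in the sentence; Follow-up restates it as allowed for all | no period stated; Follow-up puts all arms under the permissive wording |

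The trigger matches in substance. The obligation and the drug term do not. The difference is confined to the 4-week treatment period.

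**2. Inputs for an illustration of size**

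From the documents: 40 per group, two-sided 0.05, trigger at 4 days, 28 treatment days. The protocol gives no rescue uptake, SBM rate or standard deviation (SD), so there is no figure to reproduce. Assumed: the same natural SBM process in all arms (1 to 3 per week), 100% uptake on eligible days in control, and 25%, 50% or 75% elsewhere. A movement on a rescue day is not counted. The laxative is assumed not to change later bowel function.

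**3. On-treatment laxative use, no treatment effect**

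Chance of a significant excess in control = Φ(d / (SD × √(2/40)) − 1.96), with √(2/40) = 0.2236.

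Example at 2 SBMs per week and 50% uptake elsewhere: d = 0.15 and SD = 0.25, so 0.15 / (0.25 × 0.2236) = 2.68 and Φ(2.68 − 1.96) = 0.77 (0.79 with unrounded inputs).

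| SBMs per week | Laxatives per week, control v 50% arm | Chance at 50% | Chance at 75% |
|---|---|---|---|
| 1 | 0.92 v 0.72 | 0.98 | 0.34 |
| 1.5 | 0.74 v 0.56 | 0.91 | 0.25 |
| 2 | 0.58 v 0.42 | 0.79 | 0.20 |
| 3 | 0.30 v 0.21 | 0.55 | 0.13 |

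At 25% uptake elsewhere the chance is 0.98 to 1.00. With no difference between arms the formula returns Φ(−1.96) = 0.025, because it counts only the direction unfavourable to control.

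A second simulation let SBM rates vary between patients (gamma, mean 1.5 to 3 per week) and counted both directions. It gave 49–88% at 50% uptake, 17–34% at 70% and 5–7% at 90%.

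**4. The outcome as the protocol defines it**

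The outcome is a change, the baseline diary lasts one week, and the Statistical analysis section names ANOVA or the Wilcoxon test. Step 3 tests raw levels. A third simulation (gamma rates with assumed shape 2, 250 trials per setting) compared the two:

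| Uptake elsewhere | Raw level, t-test | Change from 7-day baseline |
|---|---|---|
| 50% | 35–69% | 17–34% (t-test); 19–31% (three-arm ANOVA) |
| 70% | not tabulated | about 9–12% |
| 90% | not tabulated | about 4–7% |

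The nominal rate is 5%. This assumes that rescue is also used during the baseline week, which the inclusion criteria allow by excepting emergency drugs. If nobody uses laxatives at baseline, the change equals the on-treatment level and the raw-level figures apply.

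**5. SBM and CSBM counts**

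In the step 3 model, discounted movements are 0.13 to 0.16 per week in control and 0.05 to 0.15 elsewhere. The net SBM difference is 0.01 to 0.08 per week. At the largest, 0.083 / (0.62 × 0.2236) = 0.60 and Φ(0.60 − 1.96) = 0.09; across all settings the chance is 0.03 to 0.09, against 0.025 with no difference. In the second simulation, with 60% of movements complete, the CSBM shift was 0.01 to 0.03 per week. The sign is not secure, because movements more than 24 h after a laxative count as spontaneous and the models give the laxative no effect on them.

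**The case against.** The strongest reply is that the Control group section only recaps the common rule. The Intervention section already covers control. The control text follows the same order: routine care, rescue after 4 days, recording. An arm with no intervention of its own has little else to describe. Nothing says that rescue is meant to differ by arm, the Follow-up wording is common to all, and all researchers receive standardized training. This stands as a plausible reading. A reader might infer that the protocol deliberately prescribes different rescue by arm, and the text does not support that. But it does not exclude a literal reading either: the verb is different, the drug term is different, and the other two arm sections have no matching sentence.

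A second reply is that the large false-positive rates come from assumed uptake and from raw levels instead of change. This also stands. The rates are conditional illustrations, and on change from baseline they are roughly halved when rescue is also used at baseline.

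A third is that reporting uptake by arm belongs to the analysis plan or the results. That is fair, so it is offered below only as an option.

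**Conclusion.** The two sections give different wording for the same event and must be reconciled. If the control sentence is followed literally, control can show more rescue use than the other arms with no treatment effect. The outcome at risk is mainly the change in weekly laxative frequency over the 4 treatment weeks.

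The size is unknown, because the documents give no uptake. With control always rescued, the distortion is negligible at about 90% uptake elsewhere (4–7% false positives on change, 5–7% on raw levels). At about 50% it could be material: 17–34% on change in the setting tested, and more if baseline laxative use is nil. None of these is a property of the trial as planned.

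A reader might also infer that the primary outcome is biased, since movements soon after a laxative are not counted. The figures do not support this: the shift is 0.01 to 0.03 CSBMs per week, and its direction is uncertain. The point does not threaten the pilot's main purpose, but it should be corrected because the correction is nearly free.

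**What to change.** Replace the rescue sentences under Intervention and Control group with one statement that applies to all three arms, using the same trigger, the same term for the drugs and the same wording on whether rescue is offered or given. Which clinical rule it states is for the sponsor. Remove the separate sentence from the Control group section or have it refer back to the common statement. The cost is about one paragraph of protocol text, carried through to staff training.

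Optionally, report by arm the number of trigger episodes and the share followed by laxative use. The defecation diary and the emergency-drug record (date, type and dosage) already collect the data for this, so the cost is one extra descriptive table.

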#### Follow-up

After the 4-week treatment, all participants will enter an additional 4-week follow-up period. During this time, they will receive routine health care and secondary prevention as provided to all other patients with ischemic stroke. Laxatives will be allowed for use as emergency drugs during the follow-up period. However, acupuncture treatment and mosapride citrate are not permitted during follow-up.

### Outcome measures

#### Primary outcome measure

The primary outcome measure will be the change in the weekly mean number of CSBMs over the 4 weeks of the intervention and the 4 weeks of the follow-up. A CSBM is defined as a SBM unrelated to the administration of laxatives or finger manipulation, accompanied by a self-reported feeling of complete evacuation. Bowel movements achieved with the help of glycerin, enemas, or finger manipulation are not considered spontaneous. If bowel movements occur within 24 h after the intake of laxatives, they will not be considered spontaneous. However, if bowel movements occur more than 24 h after administration of laxatives, they will be considered spontaneous. The total number of CSBMs during the treatment period and follow-up period will be averaged to obtain mean weekly CSBMs.

#### Secondary outcome measures

The change in the number of mean SBMs that are unrelated to the administration of laxatives or finger manipulation, with or without a self-reported feeling of complete evacuation. This measure will be calculated in the same way as the CSBMs.The change in mean stool consistency score, as per the Bristol Stool Scale (Table 1). The score will be recorded according to the stool type (e.g. type 1 = 1 point, type 2 = 2 points, etc.) to obtain mean stool consistency scores. The Bristol Stool Scale is a widely used form authored by Dr. K Heaton, reader in medicine, University of Bristol. It can be downloaded from the website https://www.bladderandbowel.org/bowel/bowel-resources/bristol-stool-form-scale/ representations of the different types of stool will be included in the patients’ diaries and serve as visual comparators. A patient will record the type of stool in their diary according to the picture.The change in mean straining scores during defecation. The severity of straining will be graded using a 5-point ordinal scale: 0 = absent, 1 = mild, 2 = moderate, 3 = severe, and 4 = very severe.The change in weekly frequency of laxative use. This includes the total number of times that laxatives are used during the 4-week treatment period and the 4-week follow-up period. Instances of laxative use will be summed and divided by 4 to obtain the weekly frequency during the two periods.

**Table 1 Tab1:** Bristol Stool Scale

Type	Description
1	Separate hard lumps, like nuts (hard to pass)
2	Sausage-shaped, but lumpy
3	Like a sausage but with cracks on its surface
4	Like a sausage or snake, smooth and soft
5	Soft blobs with clear-cut edges (passed easily)
6	Fluffy pieces with ragged edges, a mushy stool
7	Watery, no solid pieces; entirely liquid

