## Methods/design

### Study design

This is a prospective parallel-arm randomized controlled pilot trial comparing acupuncture with a pharmacological intervention (mosapride citrate) and usual care (control group). We will recruit patients who have sustained an ischemic stroke and present with constipation, according to predefined inclusion and exclusion criteria, between January 2017 and September 2019. Participants will be randomly allocated to one of three groups and will receive continuous treatment for 4 weeks. Repeat assessments will take place after treatment and later, at 8 weeks after inception. All participants will be asked to keep a defecation diary including weekly number of complete spontaneous bowel movements (CSBMs), SBMs, stool consistency, defecation difficulty, and laxative use and dosage, beginning at baseline during the 8-week assessment period. All outcomes will be assessed at baseline, and at 4- and 8-weeks after randomization, according to the defecation diary (Fig. 1).

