#### Recruitment and baseline assessment

Researchers will recruit participants from outpatient clinics and inpatient wards of the acupuncture and moxibustion departments. Recruitment posters will be posted in the hospital. The posters will contain a brief, Institutional Review Board-approved introduction to the study, the participants, the interventions, and contact information for the researchers. The recruitment information will also be uploaded to the hospital website (http://www.bjzhongyi.com).

Consent will be obtained by one of the investigators, with a witness present. Following written informed consent, eligible patients will be asked to complete a general information form including name, gender, age, medical history, etc. and complete a 1-week defecation diary as the baseline assessment. A neurologist will determine the Glasgow Coma Scale score and the National Institute of Health Stroke Scale score for each participant and these scores will be used to decide whether to include the patient in the study according to the inclusion and exclusion criteria. Personal information about potential and enrolled participants will be collected and maintained confidentially.

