#### Inclusion criteria

Inclusion criteria are a diagnosis of ischemic stroke according to the diagnostic criteria specified by the World Health Organization [23], constipation symptoms according to the Rome IV Functional Constipation Criteria [24], 2 weeks to 6 months after stroke onset, aged between 30 and 75 years old, Glasgow Coma Scale score ≥ 7 and National Institute of Health Stroke Scale ≤ 21, no previous medical history of constipation before stroke onset and symptoms of constipation present for at least 2 consecutive weeks after stroke, no use of gastrointestinal drugs 1 week before randomization (except for emergency drugs), no acupuncture treatment for constipation in the previous 2 weeks, and signed informed consent form.

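### Laxative use is scored as a change from a single one-week count, which adds noise; comparing the four-week frequencies with baseline as a covariate is safer (minor)

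*Protocol article*

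**What the plan says.** Under Secondary outcome measures, the protocol article defines the outcome as "The change in weekly frequency of laxative use" and gives the post-baseline scale: "Instances of laxative use will be summed and divided by 4 to obtain the weekly frequency during the two periods". That section does not say what the change is measured from. Study design points to baseline: "All outcomes will be assessed at baseline, and at 4- and 8-weeks after randomization". Recruitment and baseline assessment makes the baseline a short one, because patients "complete a 1-week defecation diary as the baseline assessment".

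Statistical analysis compares groups by Wilcoxon or ANOVA, depending on a normality test, and names no baseline covariate.

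Two further passages bear on how much laxative use the baseline week can contain. The entry rule requires "no use of gastrointestinal drugs 1 week before randomization (except for emergency drugs", so emergency use is excepted. The rescue trigger stands under Intervention: "For participants with no SBMs over 4 or more days, use of laxatives" is allowed as an emergency measure. The Control group section words it differently: "For participants with no SBMs over 4 or more consecutive days, cathartic treatment will be given".

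**The concern.** The two halves of the change score are measured with very different precision. Baseline is a whole number from 7 days; each later value is an average over 28 days. If one is subtracted from the other, the sampling noise of the single week enters the comparison in full, and neither named test takes any of it out.

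Two things are at stake. First, precision: the arms may be compared on a noisier scale than the diary data allow. Second, interpretation: a patient, or a whole arm, may seem to need more or fewer laxatives when nothing has changed. The pilot is meant to supply effect sizes and variability for a later trial, so an avoidably inflated standard deviation is unhelpful, although no passage says that the laxative figure will be used for that purpose.

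**Working it through.** **Plan's own figure.** There is none for laxative use: no rate, SD, effect or power is stated. The only checkable figure is 3 × 40 = 120 patients, which agrees.

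**Inputs from the article.** Baseline window 1 week; period values = uses in 4 weeks / 4; 40 per arm; two-sided 0.05; rescue trigger 4 or more days without a spontaneous bowel movement (SBM). Everything else below is assumed.

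**Step 1: granularity.** Baseline moves in steps of 1 per week and the period value in steps of 0.25. A patient who steadily uses laxatives at 0.5 per week scores 0.5 − 0 = +0.5 if the baseline week happened to contain no use, and 0.5 − 1 = −0.5 if it contained one. A change of zero is impossible.

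**Step 2: algebra.** Let X be the baseline-week count, Y the four-week mean, V_X and V_Y their variances and C their covariance. Then Var(Y − bX) = V_Y − 2bC + b²V_X, which is smallest at b = C/V_X. The change score fixes b = 1, the period value alone fixes b = 0, and covariate adjustment estimates the best b. Apart from the small cost of estimating b, adjustment cannot be less precise than either.

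**Step 3: Poisson example.** Assume mean rate λ = 0.7 per week, between-patient variance τ² = 0.25, and Poisson counts given each patient's rate.
- V_X = τ² + λ = 0.95; V_Y = τ² + λ/4 = 0.425; C = τ² = 0.25; best b = 0.25/0.95 = 0.26.
- Change: variance 1.25λ = 0.875, SD 0.94.
- Four-week mean alone: variance 0.425, SD 0.65.
- Adjusted: ρ² = 0.25²/(0.95 × 0.425) = 0.155; variance 0.425 × 0.845 = 0.359, SD 0.60.
- Variance ratios: 0.875/0.425 = 2.06 and 0.875/0.359 = 2.44.
- Power for an assumed difference of 0.4 per week (normal approximation, z = 0.4/(SD × √(2/40))): z = 1.91, 2.74 and 2.99, giving 0.48, 0.78 and 0.85.

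In this model the change score loses to the four-week mean alone when 1.25λ > τ² + λ/4, that is, when λ > τ².

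**Step 4: simulation of unchanged patients.** Assumptions: mean SBM rate 0.5, 1, 2 or 3 per week; between-patient CV 0, 0.5 or 1; rescue after 4 SBM-free days; 60,000 patients per setting. Two features that the article leaves open were varied: whether a rescued movement restarts the SBM-free count, and whether the count is at zero or already running when the diary opens.

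| Restarts after rescue? | Count at diary start | Most baseline uses | Mean change per week | Variance ratio, change vs period value alone | Variance ratio, change vs adjusted |
|---|---|---|---|---|---|
| Yes | zero | 1 | +0.19 to +0.38 | from 0.95 | from 1.33 |
| Yes | running | 2 | −0.01 to +0.08 | 1.40 to 10.27 | 1.91 to 10.96 |
| No | zero | 3 | +0.72 to +3.10 | 0.58 to 2.01 | 1.00 to 2.02 |
| No | running | 7 | −0.01 to +0.02 | 0.68 to 4.45 | 1.43 to 4.46 |

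Ratios below 1 against the period value alone occurred at CV 1, apart from one value of 0.98 at CV 0.5. A separate simulation with its own conventions gave 0.4 to 7 against the period value alone, 1.0 to 7.1 against adjustment, and baseline maxima of 1, 2, 4 or 7.

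Individual patients scatter both ways. With restart and a running count, 37-62% of unchanged patients seem to worsen and 27-49% seem to improve. With restart and a count starting at zero, 52-80% seem to worsen.

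**The case against.** A reader might infer something stronger: that the entry rule and the four-day trigger hold baseline use at 0 or 1, so that unchanged patients systematically seem to worsen. For a patient with no SBMs this would give floor(7/4) = 1 at baseline against (28/4)/4 = 1.75 per week on treatment, an apparent rise of 0.75. The documents do not support this as a general statement. The entry rule excepts emergency drugs, which is how the article classes the rescue laxatives. The trigger ("For participants with no SBMs over 4 or more days") stands under Intervention and is not said to govern the week before randomization. A cap at 1 also needs the count to start with the diary and to restart after a rescued movement. Movements within 24 h of a laxative are not spontaneous, so read literally a rescued movement does not restart a count of SBM-free days, and 3 to 7 baseline uses are then possible. Entry also requires at least two weeks of symptoms, so an SBM-free run may already be under way when the diary opens; the mean shift is then near zero.

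A second tempting inference is bias between arms. Baseline precedes randomization, so any mean shift is common to all arms and cancels. The analysis section names no within-arm test either.

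Two further objections stand in part. The article never spells out the subtraction, and a separate analysis plan might; but the outcome is fixed as a change, baseline is the stated first assessment, and the named tests carry no covariate. The change score can also beat the raw four-week frequency when patients differ strongly. That is true, and it is a reason to adjust for baseline rather than to discard it.

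**Conclusion.** The point holds in a limited form. As written, a coarse one-week count appears to be subtracted from a four-week mean with no baseline adjustment. In no setting tried was the change score more precise than a baseline-adjusted comparison (variance ratio 1.0 to about 11). It was less precise than the four-week frequency alone unless patients differed strongly from one another (0.4 to about 10 across all settings). The cost is lost precision and an unreliable reading of within-arm change. The between-arm comparison stays unbiased, and no 0-1 limit on baseline use can be read from the text.

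All sizes rest on assumed SBM rates, between-patient spread and rescue conventions, since the article gives no laxative data. Severity is minor: this is one secondary outcome in a pilot whose size was set for practical reasons.

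**What to change.** Define the outcome as the weekly frequency of laxative use in weeks 1-4 and in weeks 5-8, which the article already computes. Compare the arms on each value with the baseline-week frequency as a covariate, by analysis of covariance or a count model, in place of a test on the change score. Report the baseline frequency by arm, and do not interpret within-arm change from the one-week baseline. If a change is kept for description, state what it is measured from.

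The cost is the outcome wording and one sentence naming the model; no new data are needed. The downside is that this outcome is no longer expressed as a change like the other secondary outcomes.

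Separately, the investigators should reconcile the Intervention and Control group passages, one of which allows rescue while the other says that it will be given. They should also state whether the trigger applies in the baseline week and what restarts the count, since these rules shape the number being analysed.
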